## Abstract

**Background:**

Because of the implant-related problems with pedicle screw-based spinal instrumentations, other types of fixation have been tried in spinal arthrodesis. One such technique is the direct trans-pedicular, trans-discal screw fixation, pioneered by Grob for spondylolisthesis. The newly developed GO-LIF procedure expands the scope of the Grob technique in several important ways and adds security by means of robotic-assisted navigation. This is the first clinical trial on the GO-LIF procedure and it will assess safety and efficacy.

**Methods/Design:**

Multicentric prospective study with n = 40 patients to undergo single level instrumented spinal arthrodesis of the lumbar or the lumbosacral spine, based on a diagnosis of: painful disc degeneration, painful erosive osteochondrosis, segmental instability, recurrent disc herniation, spinal canal stenosis or foraminal stenosis. The primary target criteria with regards to safety are: The number, severity and cause of intra- and perioperative complications. The number of significant penetrations of the cortical layer of the vertebral body by the implant as recognized on postoperative CT. The primary target parameters with regards to feasibility are: Performance of the procedure according to the preoperative plan. The planned follow-up is 12 months and the following scores will be evaluated as secondary target parameters with regards to clinical improvement: VAS back pain, VAS leg pain, Oswestry Disability Index, short form - 12 health questionnaire and the Swiss spinal stenosis questionnaire for patients with spinal claudication. The secondary parameters with regards to construct stability are visible fusion or lack thereof and signs of implant loosening, implant migration or pseudarthrosis on plain and functional radiographs.

**Discussion:**

This trial will for the first time assess the safety and efficacy of guided oblique lumbar interbody fusion. There is no control group, but the results, the outcome and the rate of any complications will be analyzed on the background of the literature on instrumented spinal fusion. Despite its limitations, we expect that this study will serve as the key step in deciding whether a direct comparative trial with another fusion technique is warranted.

**Trial Registration:**

Clinical Trials NCT00810433

## Background

For many degenerative, inflammatory and traumatic conditions of the spine as well as for spinal deformities, the definitive fusion of one or several spinal motion segments (spinal arthrodesis) remains the treatment of choice at this time. Fusion requires the preparation of a fusion mass between two vertebrae or their posterior elements and adequate stability for the period of time that is required to achieve solid bony bridging. While there are a number of different fusion techniques, the necessary stabilization is currently almost exclusively achieved by pedicle screw - rod - systems. This technique requires 2 pedicle screws to be placed into each vertebra, which for a single-level fusion translates to 4 screws and 2 interconnecting rods. Since for every individual screw placement there is an inherent risk of implant malpositioning and nerve injury, this particular risk is encountered 4 times in a typical single-level pedicle screw construct for spinal fusion. The typical implant-related complication rates for lumbar or lumbosacral spinal fusion surgery are reported as high as 19 percent [1,2]. On the background of such complication rates and also on the basis of biomechanical considerations [3], alternative trans-pedicular trans-discal fixation techniques have been tried. Such trajectories had already been used in combination with pedicle screw and/or transvertebral cage constructs for high dysplastic spondylolistheses [4-10]. Grob and recently Zagra (using the Grob technique) were the first to use 2 trans-pedicular, trans-discal screws alone to stabilize a lumbar or lumbosacral motion segment for posterolateral fusion [11,12]. While in theory this technique reduces the risk of screw misplacement and hence of nerve injury by 50 percent per fused motion segment, they still experienced some implant-related complications requiring revision surgery. These implant misplacements were judged to be due to the difficulty of drilling the anatomically demanding screw trajectories under fluoroscopic control alone. The "Guided Oblique Lumbar Interbody Fusion" (GO-LIF) procedure overcomes these problems by means of robotic-assisted computer navigation, whose accuracy has been established [13-15]. It also expands on the original Grob procedure in 3 important ways: First, it makes minimally invasive, percutaneous screw placement possible. Second, it allows for the combination with intervertebral cage fusion techniques. And third, it doesn't require the presence of spondylolisthesis. These 3 factors greatly expand the range of possible indications. However, with less than 20 cases having been performed worldwide, it cannot yet be known whether GO-LIF might in the future represent a valid alternative to pedicle screw-based stabilization techniques. This clinical trial was designed to examine the safety and the efficacy of the GO-LIF procedure.

## Methods/Design

This is a multicentric cases series that will be compared to literature control. The study design has been reviewed and approved by the ethics committee of the Ludwig-Maximilian-University of Munich, Germany. A participant insurance policy has been provided and the trial has been registered at http://www.clinicaltrials.gov[16]. The main author is responsible for the study design, for monitoring the data collection and the anonymization as well as for the data analysis. Independent experts in spinal surgery with no association to the GO-LIF procedure or the study have committed to evaluate and judge adverse events, should any occur. These experts would then report to the ethics committee as well as to the study leaders. There are 10 participating centers in Germany, Switzerland and Italy, where a total of 40 patients are to be recruited within 6 months. We plan to present descriptive statistics and to discuss the findings on the background of the published literature.

Included will be men and women between 18 and 80 years of age, capable of giving informed consent and with a clear clinical indication for monosegmental lumbar or lumbosacral fusion (with or without decompression) based on a diagnosis of at least one item in the following list:

• painful disc degeneration (black disc)

• painful erosive osteochondrosis

• segmental instability

• recurrent disc herniation

• spinal canal stenosis

• foraminal stenosis

Exclusion Criteria are:

1) Lumbar hyperlordosis >70° between the end plate of the lumbar vertebral body 1 and the end plate of the sacral vertebral body 1 (because of the risk of injury to the facet joint below the instrumented level).

2) Deformities of the vertebral bodies envisioned for instrumentation (or the sacrum).

3) Spondylolisthesis >grade 2 (Meyerding).

4) Scoliosis and other deformities in the coronal plane (not asymmetric disc space collapse).

5) Fractures of the vertebrae envisioned for instrumentation.

6) Osteoporosis or osteopenia (known diagnosis or as assessed by DXA or qCT).

7) Therapy with systemic corticosteroids or immunosuppressants.

8) Metabolic bone diseases, such as osteomalacia or Paget's disease.

9) Post inflammatory instability of the vertebral spine.

10) Status post radiation therapy of the relevant spinal region.

11) Current Coumadin (or Warfarin) or Heparin therapy for more than 6 months at the time of operation.

12) Malignant diseases with or without bone metastases.

13) Immunologic-inflammatory diseases (e.g. rheumatoid arthritis).

14) Diabetes mellitus.

15) ongoing infectious conditions.

16) body mass index (BMI) >30.

### Operative Technique

The preoperative CT scan will be used for planning and navigation. In surgery, the SpineAssist miniature robotic device will be attached to the operating table and to the patient by means of a special bed frame and a Kirschner wire, which is anchored in a spinous process superior to the segment to be operated on (figure 1). After referencing and matching of the operative situation to the preoperative plan by means of 2 fluoroscopy images, the SpineAssist workstation will direct the miniature robotic device to the correct position. The miniature robotic device will then be fitted with one of three available arms (as prompted by the workstation), which carries a drill sleeve at its end. A support arm that is fixed to the bed mount will give additional stability so that the implant trajectory will be drilled in exactly the way it was planned (figure 2). If decompression is required, it will be performed according to microsurgical standard. In cases with a completely collapsed disc space, no interbody device is required and only bone graft may be used to fill the residual disc space if there is any. In every other case, an interbody fusion will be performed according to the surgical standards of a PLIF or TLIF procedure. Finally, the GO-LIF screw implants are placed and the procedure is ended (example shown in figure 3). While the example shown is a GO-LIF fixation at the L5/S1 level, GO-LIF can be performed at all lumbar levels. The GO-LIF fixation is not suited for spondylolisthesis reduction, which means that it can only be applied in situations of a spondylolisthesis where an in-situ fixation and fusion is planned.

**Figure 1 F1:**
[figure not shown]
**The SpineAssist miniature robotic device is mounted on a radiolucent frame, which is attached to the patient**. One of the modular arms (arm #2 in this case) is attached to the miniature robotic device and carries the drill sleeve at its end. A Steinmann pin is manually passed through the drill sleeve for demonstration purposes.

**Figure 2 F2:**
[figure not shown]
**Shows the percutaneous drilling of a GO-LIF screw trajectory, using the drill sleeve**. Lateral fluoroscopy is used to control for depth.

**Figure 3 F3:**
[figure not shown]
**3-D-reconstruction of a percutaneous in-situ fixation of a grade 2 isthmic spondylolisthesis at L5/S1 using the GO-LIF technique**.

The imaging modalities to be used in this study are plain radiographs and computed tomography (CT). The pre-operative CT, which is required to define the surgical anatomy, will be saved in such a way that it can also be used for the preoperative planning and the intraoperative navigation. A routine postoperative CT of the instrumented vertebrae will be acquired to evaluate implant positioning and to exclude intraspinal bleeding. This scan will also be used to compare the planned position of the GO-LIF implants to their real position and hence serve as a parameter for the safety of the procedure. Any implant deviations from the planned position will be measured and categorized in 1 millimeters increments. This data will be presented and discussed in full. Implants penetrating the pedicular or the vertebral cortex by more than 4 millimeters will be categorized as malpositioned according to the method by Gertzbein and Robbins [17]. Such implants will be considered unsafe in the sense of the target criterion. The plain radiographs will be used to assess construct stability, implant position, implant migration or loosening, formation of a sold fusion mass or indication of pseudarthrosis.

The following clinical data/scores will be evaluated:

• Current pre-operative analgesic treatment

• Visual Analog Scale for back pain (VAS back)

• Visual Analog Scale for leg pain (VAS leg)

• Oswestry Disability Index (ODI)

• Short Form - 36 health questionnaire (SF-36)

• Swiss Spinal Stenosis Questionnaire (SSS)

Data will be collected at the following measurement points:

1) Immediately preoperatively.

2) Intra- or perioperatively.

3) 6 weeks postoperatively.

4) 3 months postoperatively.

5) 6 months postoperatively.

6) 12 months postoperatively.

7) Thereafter, annually if after the completion of the proposed study, an extension of the follow-up period is applied for and approved.

The primary target parameters (to be assessed within the immediate perioperative phase) with regards to safety are:

• Number, severity, and cause of intra- and perioperative complications, in particular injury or irritation of nerve roots.

• Number of significant (>4 mm) penetrations of the cortical layer of the vertebral body or the pedicle by the implant, as recognized on a postoperative CT.

The primary target parameter with regards to feasibility (to be assessed within the immediate perioperative phase) is:

• Feasibility is defined as performing the intervention according to the preoperative plan. The number of interventions that could not be performed according to plan as well as the cause thereof serve as feasibility indicators.

The secondary target parameter with regards to construct stability (to be assessed on all follow-up visits until 12 months) is:

• In order to assess the stability of the GO-LIF fixation, the routinely performed functional radiographs after fixation operations will be evaluated.

The secondary target criteria with regards to clinical improvement (to be assessed on all follow-up visits until 12 months) are:

• VAS for back and leg pain, ODI and SF-36 health questionnaire and the SSS questionnaire.

We performed a power analysis in order to assess the required sample size to show safety with a power (1-β) of 0.8 and an α of 0.05. As basis for our calculation, we used the rates (5%-trimmed mean and standard deviation) of correctly placed pedicle screw implants in the best meta analysis available for such a purpose [18]. With an effect size (d) of 0.4478528 and an actual power (1-β) of 0.808629, the total sample size calculated as n = 33. Leaving some room for additional power and/or patients that might have to be excluded as a result of protocol violations, we decided upon n = 40 as the number of patients to be recruited.

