## Discussion

This is a clinical case series without a direct control and hence without randomization, which brings certain limitations to our study. Our choice of study design was influenced by several considerations. For one, since this is the "phase 1" clinical study on a new fixation technique and therefore safety and efficacy are the primary parameters to be studied, we are at this point not primarily interested in showing superiority or non-inferiority of the GO-LIF technique as compared to any other established fusion technique. It would have therefore not strengthened this first study to include another fusion technique as a comparison. This even more so, as there is no universally accepted fusion technique that everyone would agree on as the gold standard against which to compare a new technique. The power calculation for this study was rendered difficult by the following factors. On the background of the very inhomogeneous literature on spinal fusion surgery and since we expect none or few neurological complications with the use of navigation, this parameter would not have been suitable for use in our power analysis. In view of our primary target criteria, we therefore had to use a technical parameter, in this case, the accuracy of screw placement. With various classifications and with the inconstant reporting of complications in clinical trials, we resorted to the data collected and evaluated by Kosmopoulos et al. as the basis for our power calculation [18]. Even though the number of patients to be included resulted from a power analysis, it should be remembered that based on Hanley's "rule of three", even if no adverse events are to occur it cannot be concluded that such events will not happen in future patients undergoing the same procedure [19]. Depending on the outcome of this study, a prospective and randomized trial comparing GO-LIF to another fusion technique will be the next step.

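### The sample size is justified by 80% power to show safety, but the planned analysis is descriptive and the power figure belongs to a screw-accuracy mean, not to the primary safety counts

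*Protocol article*

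**What the plan says.** The final paragraph of Methods/Design gives the purpose of the calculation: "We performed a power analysis in order to assess the required sample size to show safety". Its targets are 80% power and an α of 0.05. The inputs were "the rates (5%-trimmed mean and standard deviation) of correctly placed pedicle screw implants" from a published meta-analysis; the mean and SD themselves are not given. The result reads: "With an effect size (d) of 0.4478528 and an actual power (1-β) of 0.808629", which leads to n = 33. This was raised to 40 to allow for extra power or for patients excluded after protocol violations.

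The first paragraph of Methods/Design describes the analysis: "We plan to present descriptive statistics and to discuss the findings on the background of the published literature".

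The two primary safety parameters are both counts. The first is intra- and perioperative complications, with nerve roots singled out. The second is implant penetrations of the cortex by more than 4 mm on the postoperative CT.

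The Discussion adds three things. On comparison: "we are at this point not primarily interested in showing superiority or non-inferiority of the GO-LIF technique". On the basis of the power calculation: neurological complications were judged unsuitable, so accuracy of screw placement was used instead. On the limits of a clean result: "even if no adverse events are to occur it cannot be concluded that such events will not happen in future patients", with a reference to the rule of three but no figure.

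**The concern.** Power and α are properties of a test of a stated hypothesis. A study that will only describe its results, and sets no rate below which the procedure counts as safe, has no test to which 80% power could attach. The 4 mm criterion does not fill the gap: it classifies a single implant as unsafe but does not say how many such implants would be acceptable.

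The calculation is also narrower than the claim made for it. It concerns placement accuracy, while the first-listed primary safety parameter is complications.

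The abstract presents this study as the main step towards deciding on a comparative trial. Anyone making that decision needs to know how large a complication or malposition rate 40 patients can exclude. The power statement does not answer that question, and no other figure in the article does.

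**Working it through.** **1. Reproducing the plan's own figure.** Inputs from the sample-size paragraph: d = 0.4478528, α = 0.05, target power 0.8. For a one-sample t-test, power is taken from the noncentral t distribution with n − 1 degrees of freedom and noncentrality d√n. At n = 33 this is 0.4478528 × √33 = 2.573.

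| Test | n | Power |
|---|---|---|
| One-sample t, one-sided | 32 | 0.7975 |
| One-sample t, one-sided | 33 | 0.808629 |
| One-sample t, one-sided | 40 | 0.872 |
| One-sample t, two-sided | 33 | 0.704 |
| One-sample t, two-sided | 42 | 0.809 |
| Two-sample t, 33 in total, one-sided | 33 | 0.349 |
| Two-sample t, 33 in total, two-sided | 33 | 0.238 |

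The one-sided, one-sample t-test matches to all six decimals, and 33 is the smallest n that reaches 0.8. A signed-rank calculation with an assumed relative efficiency of 1 is numerically the same calculation and gives the same figure. The arithmetic is therefore correct. It answers whether a continuous mean lies about 0.45 SD from a reference value. The article neither names that test nor plans to run it.

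**2. Setting this against the primary parameters.** Complications and penetrations above 4 mm are counts, to be summarised as rates. A standardised difference in a mean says nothing direct about either rate, and the Discussion confirms that neurological complications were left out of the calculation.

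**3. What the sample size supports per patient.** If x = 0 of n patients have an event, the exact upper limit is 1 − 0.05^(1/n) one-sided and 1 − 0.025^(1/n) from a two-sided 95% interval. The rule of three is 3/n.

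- n = 40: 1 − 0.05^(1/40) = 7.2%; 1 − 0.025^(1/40) = 8.8%; 3/40 = 7.5%.
- n = 33: 1 − 0.05^(1/33) = 8.7%; 1 − 0.025^(1/33) = 10.6%; 3/33 = 9.1%.
- One event in 40 (Clopper-Pearson): 11.3% one-sided, 13.2% two-sided.

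The chance of seeing no event in 40 patients is (1 − p)^40. For a true rate p of 2% it is 0.98^40 = 0.45; for 3%, 0.97^40 = 0.30; for 5%, 0.95^40 = 0.13.

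**4. What it supports per screw.** The article does not state the number of GO-LIF screws per patient. Assuming two, there are 80 screws. With 0 of 80 and full independence, 1 − 0.05^(1/80) = 3.7% and 1 − 0.025^(1/80) = 4.5%. Screws in the same patient share anatomy, referencing and operator, so independence is the favourable extreme. If the two screws always agreed, the effective number would be 40 and the two-sided limit would return to 8.8%. The two-sided per-screw limit thus lies between 4.5% and 8.8%, depending on the within-patient correlation.

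**The case against.** The strongest defence has three parts.

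*A test does lie behind the figure, and its details may be in a document not shown.* This stands in part. The exact reproduction shows which calculation was done, and a condensed article may leave out its name, sidedness and reference value. No fault is claimed on those omissions alone. What an unseen document cannot remove is the conflict within the article, which claims a power to show safety and also states that the analysis will be descriptive.

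*The choice of screw accuracy is disclosed and justified.* This also stands. It relates to one of the two listed safety criteria, and the Discussion explains why complications were not used. But the sample-size paragraph still claims safety in general, not screw accuracy.

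*The Discussion already warns about zero events.* It does, and it ties the warning to the power analysis. It gives no bound for n = 40, however, and leaves the power claim in place.

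Some stronger readings are tempting but not supported:

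- A reader might infer that a result with few events will be published as safety shown with 80% power. No passage says so, and the stated reporting plan and the rule-of-three caution point the other way.
- A reader might take 7 to 9% as the tightest limit the study can give. That range is per patient with 40 analysed. The screw-level limit can be lower, and with 33 evaluable patients the two-sided limit is higher.
- A reader might treat the 19 percent in the Background as an implied safety limit. It is given as the high end of reported implant-related rates, without a time window, and nothing makes it a criterion for this study.

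**Conclusion.** The point holds as a conflict between the stated justification of the sample size and the stated analysis. The calculation is arithmetically right, but it concerns a placement-accuracy mean and gives the planned descriptive analysis of complications and penetrations no power to show safety. What 40 patients offer is precision: with no events, a per-patient upper limit of 8.8% (exact two-sided 95%; 7.2% one-sided), or 10.6% two-sided with 33 evaluable. Per screw, it is at best 4.5% two-sided (3.7% one-sided), assuming two screws per patient and independence. Any observed event widens these limits.

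This should be fixed, but it does not undermine the design: a descriptive first series of 40 is coherent once it is justified as such. Neither the sample size nor the endpoints need to change.

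**What to change.** In the sample-size paragraph of Methods/Design, either limit the power statement to the screw-accuracy calculation, naming the test (by reproduction, a one-sided, one-sample t-test, for the sponsor to confirm), or withdraw it. Then justify n = 40 by precision. Wording along these lines would do:

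> The study is descriptive. Each primary rate will be reported with its denominator and an exact two-sided 95% confidence interval. If no event occurs in 40 patients, a per-patient rate of up to 8.8% (7.2% by a one-sided 95% limit) remains compatible with the data; with 33 evaluable patients the two-sided limit is 10.6%.

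For cortical penetrations, report the rate per screw with an interval that allows for screws clustered within patients. State 4.5% two-sided (3.7% one-sided) for 0 of 80 screws only as the best case under two screws per patient and independence. In the Discussion, put the figure for 40 patients next to the rule of three.

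The cost is a less favourable claim than power to show safety, and slightly more analysis for the clustered interval. Recruitment, procedures and data collection are unaffected.

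### The stated power of 0.808629 at n = 33 rests on the spread of published placement rates, which is not the variance of this trial's yes/no implant endpoint

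*Protocol article*

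**What the plan says.** The power analysis closes the Methods/Design section of the Protocol article. Its aim is to "show safety with a power (1-β) of 0.8 and an α of 0.05". For the inputs, "we used the rates (5%-trimmed mean and standard deviation) of correctly placed pedicle screw implants in the best meta analysis". The result reads: "With an effect size (d) of 0.4478528 and an actual power (1-β) of 0.808629, the total sample size calculated as n = 33". With a margin for extra power and for exclusions, "we decided upon n = 40 as the number of patients to be recruited".

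The Discussion explains the choice of parameter: "we therefore had to use a technical parameter, in this case, the accuracy of screw placement". The matching primary safety endpoint in Methods/Design is: "Number of significant (>4 mm) penetrations of the cortical layer of the vertebral body or the pedicle by the implant". The imaging paragraph of the same section sets its scale: "Implants penetrating the pedicular or the vertebral cortex by more than 4 millimeters will be categorized as malpositioned".

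The opening of Methods/Design describes a single-arm series set against the literature, with descriptive statistics. The article names no test, sidedness, reference rate or target rate.

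**The concern.** A standardised effect size is meaningful only if the standard deviation in its denominator belongs to the observations the trial will analyse. Here the denominator is described as the standard deviation of rates in a meta-analysis. Each such rate summarises a published series, so their spread shows how series differ from one another. It does not show how one patient or one screw differs from the next. The trial will observe zeros and ones, about two per patient, whose variance is fixed by the malposition rate and by the correlation between a patient's screws.

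At stake is how the result is read. The article presents the sample size as the number needed to show safety with 80% power. In a first clinical trial meant to inform whether a comparative trial follows, a clean result could be cited as coming from a study powered at 0.81 for that purpose. Nothing in the article supports that for the endpoint counted.

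**Working it through.** **Inputs from the article.** d = 0.4478528, α = 0.05, target power 0.80, stated n = 33, stated power 0.808629, 40 patients to be recruited (Methods/Design, power paragraph). Endpoint: each implant beyond 4 mm or not (Methods/Design). Two screws per segment in the parent technique (Background). That a GO-LIF patient also receives two is an inference, giving 66 screws in 33 patients and 80 in 40.

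**Step 1: reproduce the stated figure.** For a one-sided one-sample t-test, power = P(T > t₀.₉₅,ₙ₋₁), where T is noncentral t with n − 1 degrees of freedom and noncentrality d√n.

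- n = 32: noncentrality 2.533, critical value 1.696, power 0.797.
- n = 33: noncentrality 2.573, critical value 1.694, power 0.808629.

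So 33 is the smallest n reaching 0.80, and the power agrees to all six decimals. The other tests tried (two-sided, normal approximation, two-sample, Wilcoxon) do not give this pair of figures. The test is inferred, but the match leaves little doubt.

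**Step 2: put d on the endpoint's own scale.** A yes/no screw with correct-placement rate p has SD √(p(1 − p)). An improvement of d standard deviations needs a rate of p + d√(p(1 − p)). This exceeds 1 whenever p > 1/(1 + d²) = 1/1.2006 = 0.833. At an assumed p = 0.90 it is 0.90 + 0.4478528 × 0.30 = 1.034, which is impossible. If the unit is the patient's mean over two independent screws, the ceiling moves only to 1/(1 + d²/2) = 0.909. For reference rates above these ceilings, d cannot be an effect on the binary endpoint.

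**Step 3: power for the endpoint counted.** The article gives no rates, so these are assumptions. Exact one-sided binomial test, α = 0.05, screws treated as independent. The test rejects if the number of malpositions is at most c, the largest count with probability ≤ 0.05 at the reference rate.

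| Reference malposition | True malposition | c (80 screws) | Power, 80 screws | Power, 66 screws |
|---|---|---|---|---|
| 5% | 2% | 0 | 0.20 | 0.26 |
| 10% | 5% | 3 | 0.43 | 0.35 |
| 10% | 3% | 3 | 0.78 | 0.68 |
| 15% | 5% | 6 | 0.89 | 0.77 |
| 10% | 2% | 3 | 0.92 | 0.85 |

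The first row falls as screws are added because the test is discrete: c is 0 in both cases.

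**Step 4: clustering.** With correlation ρ between a patient's two screws, 80 screws carry roughly the information of 80/(1 + ρ) independent ones, from 80 at ρ = 0 down to 40 at ρ = 1. Positive correlation therefore leaves less information than the table assumes.

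**Step 5: precision.** With zero events in N independent units, the one-sided 95% upper limit is 1 − 0.05^(1/N).

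- N = 80 screws: 3.7%.
- N = 40 patients: 7.2%.

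**The case against.** The strongest reply is that nothing is miscalculated and nothing depends on the number. The printed figures are correct for the test used. The analysis is descriptive. The Discussion says the power calculation was difficult, disclaims a primary interest in superiority or non-inferiority, and invokes the rule of three to warn that an absence of events does not exclude future ones. All of this stands, and it limits the harm. It does not correct the sample-size paragraph, which still presents n as the size required to show safety at power 0.8. Nor does the rule-of-three remark repair the variance.

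Three stronger readings are tempting, and the article does not support them.

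- *The trial is underpowered.* This cannot be shown. Without a reference and a target rate, power for the implant endpoint may be below or above 0.81, as the table shows.
- *The trial falls short because α should be two-sided.* The match in step 1 shows that a one-sided test was used, and a one-sided test suits a directional aim. Leaving the word out is a reporting gap, not a deficit in power.
- *The trial could have no power at all.* That would need a patient-level endpoint tested against a 5% benchmark. The article counts implants and states no such benchmark. With 80 independent screws, zero events would reject a 5% rate (0.95⁸⁰ = 0.017).

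**Conclusion.** The point holds as a method error, not an arithmetic one. The value 0.808629 belongs to a t-test on a continuous quantity whose standard deviation is that of published rates. It is not the power of a per-implant yes/no endpoint, and the article supports no specific value in its place. Over the assumed rate pairs, power with 80 independent screws runs from 0.20 to 0.92.

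The conclusion rests on three readings: that the standard deviation of rates is a between-study spread, which is the natural sense of the wording; that the test is the one-sided one-sample t-test, inferred from the six-decimal match; and that each patient receives about two screws, inferred from the parent technique. The binomial figures also assume independent screws. The correction should be made, but because the analysis is descriptive and the article carries its own caveats, it is a should-fix item.

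**What to change.** Withdraw the statement of power 0.808629 at n = 33 and keep n = 40. Then do one of the following.

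1. **Preferred, as it suits a descriptive study:** justify n = 40 by the exact precision of the malposition rate. Give the limits in step 5 for zero events and the corresponding limits for a few events. Report the screw-level rate with an interval that allows for two screws per patient, alongside the proportion of patients with at least one breach beyond 4 mm.
2. **If a power statement is kept:** name the reference malposition rate and its source, the target rate, the unit of analysis and the one-sided α. Recompute with an exact binomial test that allows for clustering.

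The cost is a rewritten sample-size paragraph. The first option needs no extra patients, no change of endpoint and no new data. The second may show that 40 patients give less, or more, than 80% power for the rates chosen.
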